**Figure 1 fig1:**
[figure not shown]
Schedule of visits. All study subjects will be screened and enrolled at Visit 1 (at 5–12 weeks of gestation) after obtaining written informed consent. Visit 2 will be conducted between 6 and 13 weeks and Visit 3 between 8 and 14 weeks of gestation. Visit 4 will be conducted at the end of 14 weeks of gestation, with a permissible window period of +3 days. Visits 5 and 6 will be conducted at 18–20 and 24–26 weeks of gestation, respectively. Visit 7 will be conducted after parturition.

### Planned evaluations

Subjects will be screened and enrolled after obtaining written informed consent at Visit 1. Routine pregnancy-specific imaging and laboratory investigations will be done at a central laboratory during study participation. Subjects will be monitored throughout participation for AEs and serious AEs. Activities planned at each study visit are detailed in Fig. 2.

**Figure 2 fig2:**
[figure not shown]
Study flowchart. There will be a total of seven visits in this study. A detailed list of activities to be performed at each visit is presented here.

### Data collection and management

Data from source documents will be transcribed in English to case report forms (CRFs) either by the investigator or by trained and delegated clinical research coordinators; confidential details of subjects will be redacted. Accuracy, completeness and legibility of data will be ensured and then shared by the investigator in a timely manner to all those concerned. Edit checks will be run; queries will be resolved as per in-house standard operating procedures (SOPs) of the assigned Clinical Research Organization (CRO) and clarification/correction will be obtained from the investigator through data clarification forms (DCFs) in case of missing data, transcription error or new information. This will be followed by review and if data are found accurate, the database will be locked. Subsequently, data will be extracted for statistical analysis as per in-house SOPs. Relevant study documents, along with unused or spurious data, will be kept in due confidentiality for at least five years from study completion, after which these will be destroyed or retained further, as appropriate.

### Study monitoring

Monitoring will be done as per in-house SOPs of the assigned CRO to comply with the aforementioned ethical guidelines. Monitoring will include verification of subject recruitment as per eligibility criteria, source documentation, completeness and accuracy of CRFs and specified trial-related responsibilities of the investigator and trial staff, and ensure that there is no participation of unauthorized individuals in the study conduct. Adequate and accurate documents will include site master file (protocol; sample of CRF, ICF and DCF; notification, submission and approval letter of the ethics committee; staff curriculum vitae; staff job authorization forms etc.) and clinical source documents of subjects. Site participation may be terminated if noncompliance is noted. Formal site closure will be done after all study-related activities have been completed; ethics committees will be notified by the respective investigators.

### Quality assurance

Auditing will be performed as per in-house SOPs of the assigned CRO to ensure study compliance with the aforementioned ethical guidelines and to maintain the quality and integrity of data. The auditor shall be given access to all study-related documents. To ensure confidentiality, patient identification information will be concealed from copies of medical documents made for audit purposes. Findings of the auditor will be documented and informed to the study site; prompt and necessary action will be taken in case of noncompliance.

### Statistical methods

All data analysis will be carried out as per comprehensive statistical analysis plan and based on the ICH E9 document ‘Statistical Principles for Clinical Trials’. All statistical analyses will be done using the Statistical Package for Social Sciences (SPSS; IBM Corp., USA). Continuous variables will be checked for normality and analyzed using paired t-test if the distribution is normal, or Wilcoxon signed rank test otherwise. Descriptive statistics and proportions will be used to summarize the population in each treatment arm/subgroup. Categorical variables will be analyzed using McNemar’s test or Chi-square test, as applicable. Regression analysis will be used to analyze the association between variables. Incidence of AEs will be reported as the proportion of subjects reporting them.

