## Objectives

The primary objective of the study is to compare reduction in miscarriage rate before 20 weeks of gestation between the two treatment arms. The secondary objectives are to compare the following between the two treatment arms: rate of ongoing pregnancy at 24 weeks, rate of live births, safety of the study medications based on TEAEs, levels of immunomodulation markers and time to symptom resolution (Table 1).

**Table 1 tbl1:** Study objectives.

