**Secondary objectives**
• To compare the rates of ongoing pregnancy at 24 weeks and live births between women with threatened miscarriage treated with oral dydrogesterone versus oral micronized progesterone • To compare the safety of oral dydrogesterone versus oral micronized progesterone based on TEAEs in pregnant women with threatened miscarriage when treated with either • To compare the levels of immunomodulation markers, i.e., serum levels of cytokines (IL-4, IL-10, IFN-γ and TNF-α) in pregnant women with threatened miscarriage, before and after treatment with oral dydrogesterone versus oral micronized progesterone • To compare the time to symptom (vaginal bleeding and/or abdominal pain) resolution between women with threatened miscarriage treated with oral dydrogesterone versus oral micronized progesterone

TEAEs, treatment-emergent adverse events; IL, interleukin; IFN, interferon; TNF, tumor necrosis factor.

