**Secondary endpoints**
• Ongoing pregnancy rate at 24 weeks • Change in serum levels of cytokines (IL-4, IL-10, IFN-γ and TNF-α) from baseline to the end of treatment • Time to symptom (vaginal bleeding and/or abdominal pain) resolution

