### Randomization

All enrolled subjects will be randomized in a 1:1 allocation ratio to receive either oral dydrogesterone or oral micronized progesterone. A computer-generated central randomization list will be divided among the study sites. Randomization will ensure that there is equal participation of subjects aged ≤30 and >30 years, and equal participation of subjects with body mass index (BMI) ≤25 and >25 kg/m^2^ within each treatment arm. To attain this, stratified randomization technique will be used. There will be four strata within each treatment arm: (a) age ≤30 years, BMI ≤25 kg/m^2^; (b) age ≤30 years, BMI >25 kg/m^2^; (c) age >30 years, BMI ≤25 kg/m^2^; and (d) age >30 years, BMI >25 kg/m^2^.

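### For continuous endpoints the article names only paired within-woman tests, which cannot make the between-arm comparisons its objectives call for

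*Protocol article*

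**What the plan says.** The rule for continuous data is a single sentence in Statistical methods: "Continuous variables will be checked for normality and analyzed using paired t-test if the distribution is normal, or Wilcoxon signed rank test otherwise". The normality check only chooses between two paired tests.

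The same paragraph treats categorical data differently: "Categorical variables will be analyzed using McNemar’s test or Chi-square test, as applicable". That pairs a within-subject test with one for independent groups. It then adds: "Regression analysis will be used to analyze the association between variables". It also refers the analysis to a statistical analysis plan, which is not shown.

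The design and aims are comparative. Under Randomization: "All enrolled subjects will be randomized in a 1:1 allocation ratio to receive either oral dydrogesterone or oral micronized progesterone". Under Objectives: "The secondary objectives are to compare the following between the two treatment arms", with immunomodulation markers and time to symptom resolution in the list that follows. Table 1 words the cytokine objective as levels "before and after treatment with oral dydrogesterone versus oral micronized progesterone". Table 2 defines the cytokine endpoint as change "from baseline to the end of treatment". For symptoms, Table 1 states: "To compare the time to symptom (vaginal bleeding and/or abdominal pain) resolution between women with threatened miscarriage treated with oral dydrogesterone versus oral micronized progesterone". Table 2 also lists blood count, liver and kidney test changes (safety) and newborn gestational age and birth weight (exploratory).

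**The concern.** The arms consist of different women, allocated at random within age and BMI strata and not matched in pairs. A comparison between them needs a method for independent groups. The only tests named for continuous data are of the other class.

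If the sentence were applied literally, each cytokine would yield one p-value for dydrogesterone and another for micronized progesterone, and no estimate of the difference between them. Readers then tend to contrast the two p-values and take significance in one arm only as evidence of a drug difference. The Introduction presents the comparison of the drugs' immunomodulatory roles as something that earlier head-to-head studies had not explored, so the cytokine comparison is one of the trial's selling points.

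**Working it through.** The article gives no figure to reproduce here. The sample size statement concerns miscarriage and does not bear on this point. The check has three steps.

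**1. Match each endpoint in Table 2 to the tests named.**

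| Endpoint | Within-woman pair? | Named test can be computed? | Named test compares arms? |
|---|---|---|---|
| Cytokine change (secondary) | yes, baseline and end of treatment | yes, within each arm | no |
| Blood count, liver and kidney tests (safety) | yes, baseline and follow-up | yes, within each arm | no |
| Time to symptom resolution (secondary) | no, one value per woman | no | no |
| Birth weight, gestational age of newborn (exploratory) | no, one value per pregnancy | no | no |
| Miscarriage (primary), ongoing pregnancy, live birth, adverse event incidence | binary | yes, Chi-square | yes |

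The between-arm comparison is written out explicitly for cytokines and for time to symptom resolution. For laboratory and newborn values it follows from the article's general aim of comparing the two drugs and is not stated endpoint by endpoint.

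**2. What contrasting two within-arm tests would do.** Let p be the probability that a within-arm test reaches p < 0.05, and assume the same true effect in both arms. The arms are independent, so

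P(exactly one arm significant) = p(1-p) + (1-p)p = 2p(1-p).

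- p = 0.05: 2 × 0.05 × 0.95 = 9.5%
- p = 0.5: 2 × 0.5 × 0.5 = 50%, the maximum
- p = 0.8: 2 × 0.8 × 0.2 = 32%
- p = 0.9: 2 × 0.9 × 0.1 = 18%
- p = 0.99: 2 × 0.99 × 0.01 = about 2%

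The article gives no cytokine variability or effect, so p is unknown and the whole range has to be shown.

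**3. Simulation at the trial's size.** From Sample size: 152 per arm with 8% dropout gives 152 × 0.92 = 139.8, about 140 evaluable women per arm. Assumed: normal change scores with SD 1, and 10,000 simulated trials per setting.

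| True change, both arms (SD) | Exactly one paired test significant | Two-sample t-test on change significant |
|---|---|---|
| 0 | 10% | 5% |
| 0.1 | 34% | 5% |
| 0.166 | 50% | 5% |
| 0.2 | 45% | 5% |
| 0.3 | 12% | 5% |
| 0.5 | under 0.1% | 5% |

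The opposite failure also occurs. With true changes of 0.4 SD in one arm and 0.8 SD in the other, both paired tests were significant in 99.7% of trials and so showed no contrast. The two-sample test detected the difference in 91%.

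**The case against.** **The analysis plan governs.** The article condenses a fuller plan and refers to it. Had it been silent on continuous endpoints, there would be no point to make. But it is not silent: it names a class of test. An analysis plan that follows the sentence inherits the problem, and one that departs from it contradicts the published article.

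**Regression is mentioned, and ANCOVA is a regression.** True, so the text does not rule out a between-arm model. But the sentence is tied to no endpoint and not to treatment arm, so it does not supply the missing comparison. It does block one stronger inference that a reader might draw, namely that the trial will produce no treatment comparison on these endpoints and that randomisation is wasted. The article does not support that.

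**Paired tests have a proper use here.** This stands. The cytokine objective has a before/after part and the laboratory endpoints are changes from baseline. A paired test answers that part, but not the comparison of one drug with the other.

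**The percentages are not properties of this trial.** This also stands. They depend on an assumed p, and they are error rates only if discordant significance is taken as a drug difference. The article states no such decision rule.

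**Conclusion.** The sentence on continuous variables is wrong as written for between-arm purposes. It can serve within-arm description of cytokines and laboratory values. It cannot compare the arms on any continuous endpoint, and it cannot be applied at all to time to symptom resolution, birth weight or gestational age at birth. This conclusion needs no numerical assumption.

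The size of the interpretive risk does. With equal effects, and with discordant significance read as a difference, the risk runs from about 2% or less to 50% per endpoint depending on p, against 5% for a direct two-sample test.

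Two wider readings are not supported. A reader might infer that the primary comparison also lacks a valid test; it does not, since Chi-square is available for miscarriage and the other binary endpoints. A reader might also argue that within-arm change is uninterpretable because cytokines shift with advancing gestation; the article does not say so, and the point stands without it.

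This should be fixed, but it does not threaten the primary result: the affected endpoints are secondary, safety or exploratory.

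**What to change.** Replace the sentence on continuous variables with the following, and carry the same text into the analysis plan:

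- **Within-arm change:** paired t-test or signed rank test as description only, with no inference about differences between drugs.
- **Cytokines and laboratory values:** ANCOVA of the post-treatment value on arm, adjusted for baseline value and the age and BMI strata, reporting the adjusted difference with its 95% CI. A two-sample t-test or Mann-Whitney test on change is an acceptable simple alternative or sensitivity analysis.
- **Newborn birth weight and gestational age:** two-sample test, or regression on arm and strata. Baseline-adjusted ANCOVA does not apply because there is no baseline value.
- **Time to symptom resolution:** a between-arm time-to-event analysis.

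The cost is wording in the protocol and analysis plan. No new data, visits or participants are needed. Study design and settings describes the trial as still screening and enrolling, so the change can be made before results are seen.

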**Primary endpoint**
• Miscarriage rate before 20 weeks of gestation

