### Sample size

A total of 302 subjects are required to detect a difference of 5% (Siew *et al.* 2018) in miscarriage rate between the two treatment arms, with a confidence level of 95%, power of 80% and noninferiority margin of 15%, taking into account an anticipated dropout rate of 8%. The enrolled subjects will be assigned equally to the four strata (as described below) within each treatment arm; therefore, the sample size has been selected as 304. Thus, 152 subjects would be required in each treatment arm at baseline.

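### The sample size rests on a 15% non-inferiority margin, but the only analysis the article names for a categorical endpoint is a test of no difference, which does not use the margin

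*Protocol article*

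**What the plan says.** In the protocol article, Table 2 gives one primary endpoint: "Miscarriage rate before 20 weeks of gestation". It is a yes/no outcome per woman, compared between two arms randomized 1:1. Table 1 and the Objectives section say that the reduction in this rate will be compared between arms. They state no hypothesis.

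The Sample size section says "A total of 302 subjects are required to detect a difference of 5"% in miscarriage rate, "with a confidence level of 95"%, and "power of 80% and noninferiority margin of 15"%, with an "anticipated dropout rate of 8"%. This is the article's only mention of non-inferiority. The total is then raised to 304, or 152 per arm.

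The Statistical methods section defers to a statistical analysis plan that is not shown, and then lists tests by type of variable. For categorical variables the whole rule is: "Categorical variables will be analyzed using McNemar’s test or Chi-square test, as applicable". It does not mention the margin, a confidence interval for a difference, or a non-inferiority criterion.

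**The concern.** The sizing and the named analysis address different hypotheses. A non-inferiority design asks whether the data exclude dydrogesterone being worse by 15 points or more. A chi-square test asks whether the data exclude equality. Failing to reject equality is not evidence that the margin has been excluded, least of all in a trial too small to detect the 5-point difference that its own sizing cites.

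What the trial may conclude is at stake. If the named test is followed, the result does not answer the question for which about 300 women are being recruited. If the choice between the two frameworks is left until the data are seen, the primary conclusion loses its protection. The study is still enrolling, so this can be settled before database lock.

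**Working it through.** **Inputs from the Sample size section.** Total 302; difference 5 points; margin 15 points (absolute scale assumed); 95% confidence, sidedness not stated; power 80%; dropout 8%. Evaluable: 302 × 0.92 = 277.8, or 139 per arm. The event rates and the direction of the 5-point difference are not given, so every rate below is an assumption.

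**Which framework gives 302?** Since no rates are stated, the figure cannot be reproduced from the article alone. It can be back-solved.

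*Non-inferiority:* n per arm = (z₁₋α + z₀.₈₀)² × [p_T(1 − p_T) + p_C(1 − p_C)] / [0.15 − (p_T − p_C)]².
- One-sided 0.05, 15.5% against 10.5%: (1.645 + 0.842)² × (0.1310 + 0.0940) / 0.10² = 139.1, so 140 per arm; 280 / 0.92 gives 305.
- One-sided 0.025, 12.5% against 7.5%: (1.960 + 0.842)² × (0.1094 + 0.0694) / 0.10² = 140.3, so 141 per arm; 282 / 0.92 gives 307.
- Equal true rates come close to 302 only at about 26–28.5% (one-sided 0.025), or at 42.5% and above (one-sided 0.05).

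*Test of no difference:* n per arm = [1.960 √(2p̄(1 − p̄)) + 0.842 √(p₁(1 − p₁) + p₂(1 − p₂))]² / 0.05². At 5% against 10% this is 435 per arm; 870 / 0.92 gives 946. At 25% against 30% it is 1,251 per arm, or 2,720 in total. Over reference rates of 5–25% nothing comes near 302.

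The stated size is therefore compatible with a non-inferiority calculation and not with a test of a 5-point difference.

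**What the chi-square does at 139 per arm** (two-sided 0.05, uncorrected). Its power for a 5-point difference is 35% at 5% against 10%, 24% at 10% against 15%, and 15% at 25% against 30%. Exact binomial enumeration at an assumed 11% reference rate gives:

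| True rates, dydrogesterone vs progesterone | Chi-square non-significant |
|---|---|
| 16% vs 11% (5 points worse) | about 77% |
| 21% vs 11% (10 points worse) | about 37% |
| 26% vs 11% (15 points worse, at the margin) | about 9% |

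At the margin itself, a rule based on the 95% confidence limit passes 2.7% of trials at 26% vs 11% and 2.5% at 35% vs 20%. Taking non-significance as similarity would pass 9.3% and 19.3%.

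**A data set on which the two rules disagree.** Take 25/139 (17.99%) on dydrogesterone and 14/139 (10.07%) on progesterone, a difference of 7.91 points.
- Chi-square: pooled rate 39/278 = 0.1403; SE = √(0.1403 × 0.8597 × 2/139) = 0.0417; z = 0.0791 / 0.0417 = 1.90; p = 0.057 (0.084 with continuity correction). Not significant.
- Interval: SE = √[(0.1799 × 0.8201 + 0.1007 × 0.8993) / 139] = 0.0414; 95% limits 7.91 ± 1.96 × 4.14, or −0.2 to 16.0 points. Non-inferiority at 15 points fails.

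This example depends on the alpha. With one-sided 0.05 the limit is 7.91 + 1.645 × 4.14 = 14.7 points, which passes. A second example does not depend on it: 40/139 against 28/139 differs by 8.63 points with SE 5.13 and p = 0.094. Its upper limit is 18.7 points at 95%, and 8.63 + 1.645 × 5.13 = 17.1 points at one-sided 0.05.

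**How often this happens.** A non-significant chi-square together with failed non-inferiority (95% limit) occurs in about 9% of trials at 16% vs 11%, 15% at 21% vs 11%, and 35% at 30% vs 20%.

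**The case against.** The strongest reply is that the Statistical methods section is a generic list by variable type, does not name the primary endpoint, and defers to an analysis plan. The interval method, stratification and comparison with the margin are details that a condensed article may leave there. That stands as far as omission goes: a reader might infer that the trial's analysis never uses the margin, and the documents do not support that while the analysis plan is unseen. It does not remove the mismatch. The article chose to name tests, its rule for categorical variables covers a yes/no primary endpoint, and neither named test fits the stated sizing.

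Three other stronger readings should also be set aside.

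- **McNemar's test between arms.** A reader might infer that this paired test is planned for the miscarriage comparison. The sentence leaves the choice to applicability, and the study has repeated visits, so within-arm use is a fair reading. Only clarification is needed.
- **Non-significance as the expected result even when dydrogesterone is clearly worse.** At an assumed 11% reference rate this is so at 5 points (77%) but not at 10 (37%) or 15 (9%). The article also states no rule by which a non-significant result would be called similarity.
- **Significantly worse yet non-inferior as proof of the defect.** For instance, 18/139 against 8/139 gives p = 0.039 with a 95% interval of 0.4 to 14.0 points. That interval excludes zero and lies below 15, so the same double finding would arise under an interval-based analysis. It reflects the width of the margin, and with continuity correction p is 0.064.

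Finally, the Sample size section also uses the language of detecting a difference, so non-inferiority is not declared outright as the aim. This is a reason to state the hypothesis first. It does not rescue the chi-square, for which the sample is far too small at 5 points.

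**Conclusion.** The point holds in this form: the sizing uses a 15% non-inferiority margin, the only analysis named for categorical endpoints does not, and a non-significant result from it would not establish non-inferiority. The total of 302 is compatible with a non-inferiority calculation; a test of a 5-point difference would need 946 to 2,720 women over assumed reference rates of 5–25%.

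The two rules part company often enough to matter: in about 9% to 35% of trials in the three scenarios examined. These figures assume 139 evaluable women per arm, an uncorrected chi-square, an absolute margin, a 95% Wald limit and event rates that the article does not give. The frequency changes with the rates and the alpha; the mismatch of hypotheses does not. Whether the full analysis plan already resolves it cannot be judged from the article.

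**What to change.** Reconcile Table 1, Sample size and Statistical methods in the protocol article:

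1. State the primary hypothesis as non-inferiority of dydrogesterone to micronized progesterone at 15 percentage points, with the alpha and its sidedness, the assumed event rates, and the direction of the 5-point difference used for sizing.
2. Name the primary analysis: the risk difference in miscarriage before 20 weeks, dydrogesterone minus micronized progesterone, with a confidence interval at the alpha used for sizing. Accounting for the age and BMI randomization strata is preferable. The interval method is a choice among acceptable ones, but should be fixed in advance.
3. Conclude non-inferiority only if the upper limit is below 15 points. Test superiority only afterwards, from the same interval.
4. State that McNemar's test is limited to within-arm paired data.

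If the analysis plan already contains this, align the Statistical methods text with it. The cost is wording in the protocol and analysis plan, with no change to recruitment, visits or data collection. It should be done before database lock.
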